### Participant recruitment and retention

Thirty-five perinatal and mental health care providers who meet the inclusion and exclusion criteria will be recruited as participants for the training. A study team member will provide initial instructions for training course login and communicate with participants for technical issues via email. The study team will keep weekly participant log to support participant engagement and retention. Training and online assessment completion and focus group participation will be encouraged through email reminders. Participants will receive a $100 e-gift card for completing all five modules of the training and two online assessments and an additional $50 e-gift card for participating in a focus group and sharing in-depth feedback about the training, experience of using the DECIDE skills, and strategies for implementing the training as part of routine perinatal care in health systems.

### Criteria for feasibility

*Intervention uptake and engagement*: 80% or more registered participants logging in to the DECIDE for MOM Provider Training.

*Acceptability, Feasibility, and Appropriateness*: 3 (which indicates moderate agreement) or higher AFAS subscale mean scores for acceptability, feasibility and appropriateness at both immediately after the training and one-month follow-up assessments. Qualitative data collected through open-ended questions of the assessments and focus groups will be used to gain in-depth insights into perceived acceptability, appropriateness, usability including facilitators and barriers, and strategies for wide dissemination and rapid implementation of the adapted training in the real-world setting.

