##### Sample size justification

The primary aim of the study is to evaluate the feasibility and acceptability of adapted training, including recruitment, retention, training engagement, and data collection processes, rather than conduct hypothesis testing or establish efficacy. Following guidelines for sample sizes for feasibility studies [22, 23] for sufficient estimates of key feasibility parameters, the current study aims to recruit 35 participants, which is considered adequate for assessing feasibility outcomes and estimating variability in outcome measures.

Inclusion criteria:Perinatal or mental health care providers who currently provide perinatal mental health care within health systemsAges between 18 and 64Must be able to understand the training content in English and comfortably complete the assessments and share feedback in English

Exclusion criteria:Healthcare providers who do not practice as part of a health care systemHealthcare providers who do not practice in the USAHealthcare providers who do not currently provide perinatal mental health care

The study will identify potential health systems that will implement adapted DECIDE provider training. Eligible participants in the health systems will receive an email invitation that includes participation information. Health system leaders reached out by the study team will help recruit by disseminating the training information and encouraging their clinicians to take the training. For participants interested in taking part, a study team member will email further information about the study, obtain electronic consent, collect baseline data, and offer instructions for taking the asynchronous online training.

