### Intervention

Participants will take an asynchronous online DECIDE for MOM Provider Training, the adapted version of DECIDE provider training. The training will take approximately 2 h. The original core content of the DECIDE provider training [10], will be kept while clinical illustrations will be adapted to fit perinatal care settings. The five modules of the adapted DECIDE Provider Training will include shared decision-making, perspective-taking, patient activation, attributional errors, and being a responsive provider to perinatal individuals. Table 1 shows the participant enrollment, intervention and assessment timeline.

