### Outcome measures

To identify the acceptability, appropriateness, and usability of adapted DECIDE provider training, the Acceptability, Feasibility, and Appropriateness Scale (AFAS) [25] developed for the assessment of implementation outcomes for training in evidence-based practices will be used. The measure has demonstrated a good fit to the hypothesized three-factor structures (RMSEA = 0.058, CFI = 0.990, TLI = 0.987) and acceptable internal consistency (α = 0.86 to 0.91). The AFAS uses a 5-point Likert scale with 1 indicating “not at all” and 5 indicating “extremely.” A few examples of the items are: “To what extent are you satisfied with the training you received and the practices covered?”, “How comfortable are you with the practices contained within the training?”, “How well do the information and practices fit with your overall approach to service delivery and the setting in which you provide care?” AFAS has demonstrated sensitivity to assessing workshop-specific perceptions about training acceptability and feasibility [25].

Open-ended questions will be added to obtain detailed information on user acceptability, appropriateness and usability. The example questions include the following: (1) Share your experience of taking the asynchronous online training regarding login, course navigation, module organization, and other aspects of accessing the training (2) Did the training change how you interact with perinatal individuals with mental health disorders? What are the specific examples? (3) What are the best strategies to effectively implement the DECIDE for MOM Provider Training within your organization?

The online assessment of acceptability, appropriateness, and usability will be conducted immediately after and one month after the training. Considering that immediately measuring acceptability, appropriateness, and usability can increase the correlation between appropriateness and usability but less highly correlated post-implementation of an intervention as providers perceive usability differently once they actually use the skills taught, [26] providers who complete the training will be asked to also participate in the one-month follow-up assessment.

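### The uptake and engagement criterion counts only logins, so it measures uptake but not engagement with the five-module training

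*Protocol article*

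**What the plan says.** The Sample size justification section of the protocol article gives the primary aim as to "evaluate the feasibility and acceptability of adapted training, including recruitment, retention, training engagement, and data collection processes". The planned size is stated there too: "the current study aims to recruit 35 participants".

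The Intervention section describes five modules and adds: "The training will take approximately 2 h".

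The Criteria for feasibility section sets two quantitative criteria:

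- Under a label that names both uptake and engagement, the rule is: "80% or more registered participants logging in to the DECIDE for MOM Provider Training".
- For the AFAS questionnaire, the rule must be satisfied at each of the two assessments and is: "3 (which indicates moderate agreement) or higher AFAS subscale mean scores for acceptability, feasibility and appropriateness".

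Three other statements bear on the point:

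- Outcome measures says who is approached at one month: "providers who complete the training will be asked to also participate in the one-month follow-up assessment".
- Participant recruitment and retention sets the payment: "Participants will receive a $100 e-gift card for completing all five modules of the training and two online assessments".
- The recruitment text under Sample size justification says that, for interested providers, a team member will "obtain electronic consent, collect baseline data, and offer instructions for taking the asynchronous online training". The term *registered* is not defined there or elsewhere in the article.

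**The concern.** The criterion's label covers two things, uptake and engagement, but its metric covers one. Opening the course shows that a provider gained access. It does not show how much of the training was received. No module count, time spent or completion share enters the rule, and retention, also part of the primary aim, has no criterion at all.

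This matters because the process adaptation under study is asynchronous delivery, chosen to lighten the load on providers. Stopping partway through the modules is a direct quantitative sign that this has not worked, and this criterion cannot register it. The Discussion says the findings will inform a future large-scale evaluation. A report that the engagement criterion was met could then be read as evidence that providers take the training to the end, which the criterion does not test.

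**Working it through.** **Inputs from the protocol article.** N = 35 (Sample size justification). Threshold 80%, event = logging in (Criteria for feasibility). Full training = five modules (Intervention). The article gives no derivation of the 80% and no expected login or completion rate, so there is no calculation of the plan's own to reproduce.

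**Step 1: the threshold as a count.** 0.80 × 35 = 28 logins. An observed 28/35 = 80% has an exact (Clopper-Pearson) 95% interval of 63% to 92%.

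**Step 2: does completion enter the rule?** Let L be the number logging in and C the number completing all five modules, with C ≤ L. The rule is L ≥ 28. C does not appear. At L = 28 the criterion is met for every C from 0 to 28, that is, from 0% to 28/35 = 80% of participants completing. At L = 35 it reads 100% for every C from 0 to 35.

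**Step 3: can the rule fail?** Yes. With X ~ Binomial(35, p) and p an assumed true login rate, P(X ≥ 28) is:

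| Assumed login rate p | Chance the criterion is met |
|---|---|
| 80% | 0.60 |
| 90% | 0.98 |
| 95% | 0.9997 |

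These chances depend only on p. They do not change with completion.

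**Step 4: how far can login and completion diverge?** For illustration only, assume a login rate of 95% and vary the completion rate among those who log in (c). Overall completion is 0.95 × c. The last column applies the same 28-of-35 mark to completion, purely for comparison.

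| c | Overall completion | Expected completers (35 × 0.95 × c) | Login rule met | Same mark on completion met |
|---|---|---|---|---|
| 50% | 47.5% | 16.6 | 0.9997 | 0.0001 |
| 80% | 76% | 26.6 | 0.9997 | 0.37 |
| 90% | 85.5% | 29.9 | 0.9997 | 0.88 |

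None of these rates comes from the article. The table shows only that the two measures can give different answers.

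**Step 5: does the AFAS criterion supply the missing test?** It requires subscale means of at least 3 at both time points and states no minimum number of respondents. The one-month assessment is directed to those who completed the training. If nobody completed, there would be no one-month mean and this criterion could not be met. With even one completer who responds (1/35 = 2.9%), a mean formally exists. So the two criteria together require some completion, but no stated amount.

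**The case against.** The strongest defence has five parts.

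- *Login is a real test.* Never opening a self-paced course is a genuine failure of uptake, and at a true login rate of 80% the rule would fail about four times in ten (1 − 0.60). This stands. A reader might infer that the rule tests almost nothing, but Step 3 shows otherwise. The defect lies in the engagement half of the label.
- *Low completion is unlikely.* The $100 is paid for finishing the modules and both assessments, not for logging in, and the email reminders are aimed at completion. This also stands: the article gives no reason to predict poor completion. But incentives and reminders are not criteria, and whether providers finish is part of what a feasibility study should find out.
- *The study has other ways to see trouble.* Open-ended questions ask about login, navigation and module organization, focus groups explore barriers, and the analysis puts its emphasis on the qualitative data. So the study as a whole is not blind to failure of the asynchronous format. The gap is in the quantitative criterion.
- *The consequences are limited.* The study is single-arm and descriptive, with no hypothesis test and no stated stop/go rule. Completion can still be reported as counts and percentages. This lowers the severity, but reporting completion alone would not change whether the engagement criterion is declared met.
- *An article condenses the full protocol.* That would answer a complaint about something left out. Here the article itself states the criterion, its threshold and its label.

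A reader might also infer that registered participants have all consented and given baseline data, so that the denominator is already selected for willingness. The article does not say when a person becomes registered. What it supports is that the term needs a definition, not that the denominator is biased.

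**Conclusion.** The point holds in a limited form. The criterion measures uptake, and its result is unaffected by how many of those logging in complete the five modules: at the 28-login mark, completion can lie anywhere from 0 to 28 of 35. The AFAS criterion narrows this only by requiring some completers to exist at one month. Training engagement and retention, both in the stated primary aim, therefore have no threshold that measures them.

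This conclusion rests on the literal wording. The text gives no frequency or depth of login, so one login per person suffices as written. It does not rest on any assumed completion rate. The size of any practical discrepancy cannot be known from the article, and no particular shortfall is predicted.

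It should be corrected, ideally before results are assessed. It is not a reason to regard the study as unsound, given its descriptive purpose and the absence of a stop/go rule.

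**What to change.** 1. Keep the 80% login rule and label it uptake only.
2. Define *registered*, for example as all consented participants, so that the denominator is fixed in advance.
3. Add a separate engagement criterion: the percentage of all consented participants who complete all five modules. The sponsor should prespecify and justify the threshold. Nothing in the article supports carrying the 80% over from login.
4. Report the number of AFAS respondents beside the subscale means at each time point, so that a reader can see how many people each mean rests on.
5. Record module completion separately from assessment completion. The e-gift card depends on both, so module completion must already be ascertained. A payment record alone would miss someone who finishes the modules but not the one-month form.

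Uptake among all invited providers is not requested: health system leaders help to spread the invitation, so that denominator may be unknown.

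The cost is a completion figure that cannot exceed the login figure on the same denominator and will probably look less favourable, a separate completion record if one is not already kept, and a protocol modification approved by the IRB. The sample size and the assessments need not change.

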### Mixed-methods data analysis

All quantitative data will be collected and stored in a secure HIPAA-compliant Qualtrics database. All focus groups through Zoom will be transcribed through Zoom Caption and verified by the study team. Downloaded data for analyses will be stored in a HIPAA-compliant, password-protected Box folder. Descriptive statistics will be used to summarize quantitative data elements (e.g., provider demographics, years of experience in perinatal mental health care, number of months at the current job, and acceptability, appropriateness, and usability scores). Continuous variables will be summarized as means (standard deviation) if normally distributed, or median (range) for skewed data. Categorical data will be summarized as counts and percentages. Qualitative data from the focus groups will be analyzed using a deductive coding approach by creating pre-defined codes and then developing additional nodes from the participant recommendations. For the training participant data which will include both quantitative and qualitative data, the mixed-method data using a sequential structure, with an emphasis on the qualitative data (quanQUAL) will be used [27].

### Data monitoring

As this study is a small-scale feasibility study, no formal data monitoring committee will be convened. There is no harm anticipated as a result of taking part in this study other than discomfort. The online assessments will collect participant names and IP addresses. Upon downloading the assessment data, identifiers will be separated from the data. We will create IDs for participants to create a link to identifiers. The link will be stored in a HIPPA-compliant, password-protected Box folder. The Principal Investigator and the Research Assistants will have access to the data. Once the Zoom recordings are moved to the HIPPA-compliant Box folder, the study team will remove the recordings from Zoom. Identifying information linked to individual subject data will be removed after manuscripts on the study are published. The de-identified data will be maintained for six years after the completion of the study.

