*Create, record, edit, and upload the adapted DECIDE provider training in Canvas*: Gathering stakeholders’ input, the investigators will adapt training content, develop scripts for vignettes, revise the training content and scripts through the iterative process of reviews and revisions by engaging the provider advisory board and the subject matter experts, and record training modules in Zoom webinars. Video clips for clinical illustrations created based on the scripts will be inserted into the adapted DECIDE provider training. This recorded asynchronous training will be edited and uploaded in a Canvas course.

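### AFAS ratings, one of the two feasibility criteria, are collected under participants' names and IP addresses and are open to the team that adapts the training; ID-coded links would be a cheap improvement

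*Protocol article*

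**What the plan says.** The Outcome measures section of the protocol article makes the AFAS the instrument for rating the training. Participants complete it themselves on a five-point scale, online, once straight after training and again a month later. Open-ended questions are added to it.

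Under Criteria for feasibility there are two quantitative criteria. One is log-in by at least 80% of those registered. The other is "3 (which indicates moderate agreement) or higher AFAS subscale mean scores for acceptability, feasibility and appropriateness", to be met at both assessments.

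Data monitoring says of the same assessments: "The online assessments will collect participant names and IP addresses". It continues: "Upon downloading the assessment data, identifiers will be separated from the data", and "We will create IDs for participants to create a link to identifiers". The link file goes into a password-protected folder. On access it says: "The Principal Investigator and the Research Assistants will have access to the data".

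The Phase 1 section assigns the building of the training to the study's own investigators: "the investigators will adapt training content, develop scripts for vignettes, revise the training content and scripts". The recruitment text under Sample size justification adds that health system leaders will help by "encouraging their clinicians to take the training".

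**The concern.** The AFAS asks for opinions, such as how satisfied the provider is with the training. Providers give these opinions in a form that carries their name, to a team that includes the people who made the product being rated. That setting invites courteous answers.

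Two features of the design let such a shift reach the result. There is no comparison arm in which the same courtesy would cancel, and the criterion is an absolute cutoff. The shift would run in one direction, toward declaring the training acceptable, feasible and appropriate.

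The safeguards in the article act on the data file. Identifiers come off when the data are downloaded, by which time the respondent has already answered knowing that a name is attached. This protects confidentiality but cannot restore candour. The open-ended answers sit in the same named survey and are exposed in the same way. The findings are meant to inform whether a large-scale evaluation follows, so a borderline training that passes on courtesy would carry that error forward.

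**Working it through.** **The plan's own figures.** No stated figure is in dispute. The target of 35 rests on guidance for feasibility studies, without an SD, a precision target or a test, so there is nothing to reproduce for this point. The log-in criterion amounts to 0.80 × 35 = 28 providers if all 35 register. The AFAS criterion covers 3 subscales × 2 time points = 6 means, each of which must reach 3.

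**Tracing the rating.**
1. The AFAS is part of the online assessments (Outcome measures).
2. Those assessments record name and IP address (Data monitoring).
3. The Principal Investigator and Research Assistants can read the data (Data monitoring), and the investigators adapt and script the training (Phase 1). The article does not say whether the Research Assistants write content.
4. Separation happens on download, after step 2, and the team keeps the link file.

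**What a shift would do.** These inputs are assumptions and are not in the article: SD of the ratings 0.6 to 1.0, candid mean μ, upward shift b, and all 35 providers responding. For one subscale at one time point,

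P(observed mean ≥ 3) = 1 − Φ((3 − μ − b) / (SD/√35)).

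Worked case, SD 0.6 and μ = 2.8: the standard error is 0.6/√35 = 0.101. Without a shift z = 0.2/0.101 = 1.97 and P = 0.024. With b = 0.2, z = 0 and P = 0.500.

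| SD | μ = 2.8, b = 0 | μ = 2.8, b = 0.2 | μ = 2.6, b = 0.2 | μ = 3.5, b = 0 |
|---|---|---|---|---|
| 0.6 | 0.024 | 0.500 | 0.024 | 1.000 |
| 0.8 | 0.070 | 0.500 | 0.070 | 1.000 |
| 1.0 | 0.118 | 0.500 | 0.118 | 0.998 |

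A 0.2-point shift matters for a training just below the cutoff. It does little for one that is clearly below it (μ = 2.6) and nothing of note for one that is clearly above it (μ = 3.5).

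A larger sample would not remove the problem, because b does not shrink with n. Requiring all six means to pass lowers the overall chance of passing. It is weak protection against this bias, though, because a courtesy shift common to respondents would raise all six together.

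**The case against.** The strongest reply is that the article contains no error here. It describes openly how identifiable data are handled, and nothing elsewhere contradicts it. Linked responses have a purpose: two assessments a month apart, reminders, and a gift card for completing the modules and both assessments. Payment depends on completion, not on scores. All of this stands, but the purpose needs a participant ID, which the study already creates, and not a name or IP address in the rating form.

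A second reply is that ID-coded links do not make raters unidentifiable while the same team holds the key. That is right, and it is why the fix moves the key to someone outside training development. Focus groups on Zoom stay identifiable whatever is done.

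Several stronger readings are tempting, and the documents do not support them.
- A reader might infer that the AFAS alone decides feasibility. It is one of two quantitative criteria, and log-in is not self-report. Log-in measures access, however, so it cannot correct inflated opinions.
- A reader might infer that health system leaders see individual answers. The article says only that they spread information and encourage clinicians to take part. Access is given to the Principal Investigator and Research Assistants, and no proportion of leader-encouraged participants is stated.
- A reader might infer that respondents are told nothing about who sees their answers. Consent and survey wording are not shown, so this cannot be established.

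**Conclusion.** The point holds as a minor design limitation. The article fixes a named survey for a subjective rating, gives access to members of the team that adapts the training, and judges the result against an absolute cutoff without a comparator. Any social-desirability shift would favour passing, and separation on download comes too late to prevent it.

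Its size is unknown. It would be wrong to say that the scores are inflated: that is an inference from the setting, and the article gives neither an expected mean nor an SD. The tabulated probabilities rest wholly on assumed values and apply to one subscale at one time point. They show only where the bias could change the conclusion, namely with candid means near or below 3.

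**What to change.** Collect both assessments through individual Qualtrics links that carry only the study ID, with no name field and with IP recording switched off. Have an existing team member who is not involved in developing the training hold the ID-to-name file and use it for linkage, reminders and gift cards. Tell respondents accurately that answers are coded, and who can and cannot see them. Do not promise anonymity, because the key exists.

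The cost is small: individual links instead of one open link, and an institutional review board approval, which the article already requires for protocol modifications. No extra participants or staff are needed. Because focus groups remain identifiable and coded answers can still be traced through the key, acknowledge the residual bias when interpreting the AFAS criterion, especially if any subscale mean falls close to 3.
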